## **5 Data management**

### **5.1 Data collection**

Data collected from participant charts and during phone interview will be recorded by research personnel in a web-based Case Report Form created using the secure platform: REDCap. Each participant will be identified by a unique ID number.

Details regarding delivery, obstetrical history, and information on the baby will be abstracted from the charts.

Information from the clinic visits including referrals will be abstracted from the clinic charts.

Data will also be collected by the means of surveys sent to the mother. Participants completing surveys online will receive a link by E-mail to complete the surveys. Upon clicking on the "submit" button the survey will be sent to research database and will no longer be available to the participant.

### **5.2 Database security**

REDCap (Research Electronic Data Capture) is a secure, web-based application designed exclusively to support data capture for research studies. REDCap provides: 1) an intuitive interface for data entry (with data validation); 2) 128 bit encryption between the data entry client and the server (https); 3) audit trails for tracking data manipulation and export procedures; 4) automated export procedures for seamless data downloads to common statistical packages (SPSS, SAS, Stata, R); 5) procedures for importing data from external sources; and 6) advanced features, such as branching logic and calculated fields.

REDCap is developed and maintained by a team at Vanderbilt University and licensed free of charge by the Research Institute at the Children's Hospital of Eastern Ontario (CHEO). The application and data are housed on servers provided by CHEO. These servers are located within CHEO's secure data center. Local support for REDcap is provided by CHEO's Clinical Research Unit.

CHEO's Clinical Research Unit Data Coordinating Centre (DCC) will be used as a central location for data processing and management. The DCC will house the data in a dedicated, locked server room within the CHEO Hospital main site, which is secured with limited badge access security cameras and 24-hour on-site security guards. The DCC coordinates its network infrastructure and security with CHEO Information Systems (CHEO IS). This provides the DCC with segregated and redundant firewalls and switches, HVAC, malware and anti-virus support, data backup and recovery support, and server hardware and software support within CHEO IS. Network equipment includes two servers connected to redundant gigabit switches. Administrative user authentication to the servers is centralized to CHEO IS Active Directory while the application authentication uses an internal table-based authentication method. Communication over public networks and between the web application and the database is encrypted using secure socket layer (SSL) with 256-bit encryption or higher.

For participants who prefer electronic follow-up, a link to a secure, web-based questionnaire will be sent to a personal email address provided by the participant. E-mail addresses will be entered and stored directly in the study database on a discrete instrument (page) within the project. Access to this page will be restricted to study team members who are responsible for inputting the address and sending the questionnaire. Any study team member who requires access to the dataset but does not need to view/input the e-mail address will be assigned "No Access" to the page. E-mail addresses will not be printed or exported at any time. Furthermore, all study team members will be granted "De-Identified" access for Data Export to ensure that e-mail addresses are never exported. As with all data entered into the REDCap database, e-mail addresses will be stored on servers in CHEO's secure Data Center within the hospital main site.

The investigators and DCC staff are fully committed to the security and confidentiality of all research data. All DCC personnel have signed confidentiality agreements concerning all data encountered in the center. Violation of these agreements may result in termination from employment at the CHEO Research Institute. In addition, all personnel involved with DCC data systems have completed GCP training and are governed by DCC standard operating procedures that address data management, privacy and security

## **6 Ethical considerations**

### **6.1 Ethics committee**

The study may only be initiated after the Investigator has obtained written approval of the protocol, Informed Consent form and other study documents, and any amendments (if applicable), by the Ottawa Health Science Network Research Ethics Board (OHSN-REB). Changes in protocol (amendments) must be submitted to the OHSN-REB for approval. The Investigator will submit reports on, and reviews of, the trial and its progress to the OHSN-REB at the intervals according to their guidelines. The principal investigators ([name] and MW) will review each of the cases requiring hospital readmission within 15 days after discharge, and after each 200 new enrolled patients, a summary of the recruitment and the number of readmission will be forwarded to a Data Safety Monitoring Board (DSMB). The DSMB will consist of one statistician, one paediatrician (or neonatologist), and one family physician with expertise in obstetrics.

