## 2.2 Hypothesis

We hypothesize that women discharged within 24 ( $\pm 12$ ) hours post vaginal delivery or 48 ( $\pm 12$ ) hours post-Caesarian section) and referred to the post-partum clinic will show a higher rate of exclusive breastfeeding at 3 months post-delivery than those who do not participate in this follow-up program (women from this study and from the previous pilot study). Our secondary hypothesis relates to the use of resources and the economic impact of the clinic. We believe that there will be fewer neonatal emergency room visits, fewer hospital readmissions and an overall decrease in the use of hospital and healthcare resources from the new mothers attending the breastfeeding clinic. This will lower the costs associated with these resources and help increase bed availability at hospitals and medical centers. We also hypothesize that women attending the clinic will be more satisfied and that the sustainability of this clinic and transferability to other settings will be feasible.

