## 2.4 Secondary Outcomes

1. Rates of hyperbilirubinemia requiring phototherapy or hospitalization
2. Poor infant weight gain requiring intervention (pumping, supplementation, hospitalization)
3. Incidence of breastfeeding difficulties (e.g., sore nipples, insufficient milk supply, inadequate latch, engorgement)
4. Breastfeeding self efficacy score (Breastfeeding Self Efficacy Scale or BSES) at 2 weeks, 1 month and 3 months
5. Score of the Edinburgh Post-partum Depression Scale for new mothers
6. Access to community-based services: Public Health Clinics, Family Doctor, Pediatrician
7. Number of emergency department visits for the mother and the baby
8. Number of hospital readmissions for the mother and her baby
9. Mothers' satisfaction with the support received
10. Length of stay in the hospital, from delivery to discharge
11. Costs associated with this community-based postpartum clinic.

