### **3.3 Non-intervention arm post-discharge events**

Women randomly assigned to the non-intervention arm option will be discharged according to the current hospital standards, in accordance with their physician or midwife's decision. After hospital discharge, the participant and her baby will be entitled to receive follow-up care and seek breastfeeding support that is currently available in the community (e.g. through their family doctor, Public Health Unit or private services), but may not attend the pilot breastfeeding clinic.

Women will be contacted at 2 weeks, 1 month and 3 months post-delivery to complete the different surveys and questionnaires (3.5).

As is current standard of care practice, women will be assessed by Public Health Nurses for post-partum depression shortly after birth. Services will be provided as per the standard.

As part of the research, women will be contacted by phone at 3 weeks by a Public Health Nurse to administer the Edinburgh Postnatal Depression Scale. In the event of a high score, the Ottawa Public Health Nurse will provide the participant with appropriate support. Information collected will be abstracted by the research staff.

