### **3.4 Intervention arm post-discharge events**

Women randomly assigned to the intervention will be discharged approximately 24 hours following a vaginal delivery or approximately 48 hours following a C-section. While this is the aimed ideal time of discharge, there may be variation as time of discharge will ultimately depend on the attending physician/midwife's opinion/orders and what he/she feels is in the best interest of the mother and her newborn. Women who choose to stay in the hospital longer will still be referred to the Monarch Clinic and will not be excluded from the study.

Women and their infants will be expected to attend a pre-booked appointment at the breastfeeding clinic, scheduled within 48 hours of their discharge. Clinic staff will follow up with the participant if she fails to keep the mandatory follow-up appointment. This first appointment will include maternal assessment and care (e.g., wound care, prescriptions), neonatal care (e.g., tongue-tie clips, jaundice screening using transcutaneous bilirubinometer), blood work including TSB (samples couriered to TOH central laboratory, HBHC postpartum assessment, and breastfeeding assessment and support. Family physicians will be available for on-site consultations in the mornings, and lactation consultants and registered nurses will be at the clinic throughout the day from Monday to Friday and Saturday mornings. Medical data (e.g., bilirubin level (transcutaneous and serum), newborn assessment, infant weight gain, urination and defecation frequency, breastfeeding assessment and progress, maternal care) found in the clinic chart will be gathered.

The Bilirubin Pathway, established by the CMNRP, will be used to guide for the management of neonatal jaundice. Those guidelines provide recommendation for subsequent TSB and or TCB follow-up, according to the modified Buthani's normogram and whether risk factors for hyperbilirubinemia are

present or not. For babies discharged before 24 hours, blood for the newborn screening will be drawn at the first visit and sent by mail to the Newborn Screening Ontario laboratory located at CHEO.

Additional follow-up visits at the breastfeeding clinic will be made available to participants for the month following the birth of their baby.

Participants in the intervention group will also be contacted at 2 weeks, 1 month and 3 months to complete the different surveys and questionnaires (3.5).

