### 3.8 Study calendar

| Events \ Timing                                                        | Day of Delivery - Screening (Day 0) | Day after discharge (Day 1-2) | Between Day 1-Day 30 (Additional Visits-Optional) | Day 14 | Day 21 | Day 30 | Day 84 | Day 180 |
|-------------------------------------------------------------------------------|-------------------------------------|-------------------------------|---------------------------------------------------|--------|--------|--------|--------|---------|
| Informed consent                                                              | X S                                 |                               |                                                   |        |        |        |        |         |
| Eligibility Confirmation                                                      | X S                                 |                               |                                                   |        |        |        |        |         |
| Ask for contact information                                                   | X S                                 |                               |                                                   |        |        |        |        |         |
| Randomization                                                                 | X S                                 |                               |                                                   |        |        |        |        |         |
| Collection of information about delivery, obstetrical and medical history and | X S                                 |                               |                                                   |        |        |        |        |         |

|                                                                                                                                     |   |   |   |     |     |     |     |     |
|-------------------------------------------------------------------------------------------------------------------------------------|---|---|---|-----|-----|-----|-----|-----|
| information on the baby from hospital chart                                                                                         |   |   |   |     |     |     |     |     |
| Hospital discharge within 24 hours for vaginal birth and 48 hours for C-section                                                     | X |   |   |     |     |     |     |     |

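### Readmissions can only start at discharge, which allocation sets earlier in the clinic arm; a count of hospital treatment from a common origin should be added beside them

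*Protocol*

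**What the plan says.** **The outcome.** Protocol section 2.4 lists, as secondary outcome 8, "Number of hospital readmissions for the mother and her baby". It gives no time origin and no window. Section 2.2 expects that "there will be fewer neonatal emergency room visits, fewer hospital readmissions and an overall decrease in the use of hospital and healthcare resources".

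**The safety review.** Under section 6.1 the principal investigators "will review each of the cases requiring hospital readmission within 15 days after discharge". After each 200 enrolments the number of readmissions goes to the DSMB. This is the only place where a readmission window is stated.

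**Discharge by arm.** Section 3.4: "Women randomly assigned to the intervention will be discharged approximately 24 hours following a vaginal delivery or approximately 48 hours following a C-section". The same section calls this an aim that the attending clinician or the mother may vary. Section 3.3: "Women randomly assigned to the non-intervention arm option will be discharged according to the current hospital standards", with no hours given. In the section 3.8 calendar the row "Hospital discharge within 24 hours for vaginal birth and 48 hours for C-section" is marked for the clinic arm only. Section 3.2.2 places randomisation before discharge, and section 2.1 makes a shorter stay an objective.

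**Neighbouring outcomes and data.** Outcome 1 covers hyperbilirubinaemia treated by phototherapy or in hospital. Outcome 2 covers poor weight gain that needs intervention, and outcome 10 is length of stay from delivery. The birth-chart items in section 3.2.1 include bilirubin, supplementation, and the date and time of discharge. They do not list phototherapy or other treatment given.

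**The concern.** Nobody can be readmitted before being discharged. Here discharge is a post-randomisation event whose timing is part of what is allocated, so the two arms become at risk of a readmission at different infant ages. Take two infants with the same problem at the same age, arising after the clinic-arm discharge time but before controls usually leave. The one in the clinic arm returns to hospital and is counted. The one in the control arm is treated where he or she already is and is not counted as a readmission.

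Section 1 itself says that feeding difficulties can lead either to longer stays or to early readmissions, through jaundice, dehydration and poor weight gain. The same morbidity can thus appear under either heading, and the arm influences which. At stake are the hypothesis of fewer readmissions, where a real benefit could be masked, and the DSMB count, where the clinic arm could look less safe than it is.

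**Working it through.** The plan states no figure to reproduce, so the check is one of logic, followed by an illustration on assumed values.

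**Step 1. Which events are affected.** Let *d* be the gap between the clinic-arm and control discharge times. Only problems that arise within *d* are classified differently by arm. If *d* = 0, nothing changes.

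**Step 2. Windows of infant age.** Under the 15-day rule of section 6.1, with discharge at 24 hours in the clinic arm and an assumed 48 hours in controls, the windows cover ages 1 to 16 days and 2 to 17 days. Controls lose the first *d* and gain a later *d* at the end. The net difference is the events in the first *d* minus the events in the *d* that follows day 15 after the clinic-arm discharge. It goes against the clinic arm whenever early events are the more frequent.

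**Step 3. Uniform event rate.** Both arms have 15 days at risk, so the net shortfall in controls is 0.

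**Step 4. Declining event rate.** Assume the same morbidity in both arms and an exponential decline with mean *T* days from the clinic-arm discharge time.
- Clinic arm: 1 − exp(−15/*T*).
- Control arm: exp(−*d*/*T*) − exp(−(*d*+15)/*T*) = exp(−*d*/*T*) × [1 − exp(−15/*T*)].
- Shortfall in controls: 1 − exp(−*d*/*T*).

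| *T* (days, assumed) | *d* = 12 h | *d* = 24 h |
|---|---|---|
| 2 | 1 − exp(−0.25) = 22.1% | 1 − exp(−0.5) = 39.3% |
| 3 | 1 − exp(−0.167) = 15.4% | 1 − exp(−0.333) = 28.3% |
| 4 | 1 − exp(−0.125) = 11.8% | 1 − exp(−0.25) = 22.1% |
| 5 | 1 − exp(−0.1) = 9.5% | 1 − exp(−0.2) = 18.1% |

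**Step 5. What a shortfall does to the comparison.** With a shortfall *g*, the spurious ratio of clinic to control readmission rates is 1/(1 − *g*): 1.11 for *g* = 10% and 1.33 for *g* = 25%. With the planned 306 and 154 women (section 4.1), an assumed 4% incidence and *g* = 25%, identical morbidity gives 306 × 0.04 = 12.2 expected readmissions in the clinic arm and 154 × 0.04 × 0.75 = 4.6 in controls, or 4.0% against 3.0%.

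**Step 6. Outcome 8 if follow-up ends at a common age.** The section 3.8 calendar counts from delivery and has its last resource survey at Day 84. With discharge at Day 1 in the clinic arm and a 24-hour gap, a uniform rate gives 1/83 = 1.2%. Under the declining rates the figures in the table hold almost unchanged, because nearly all events have occurred well before Day 84.

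**Step 7. Counting from a common origin.** If treatment is counted from randomisation to a fixed day after birth, whether in the birth stay or on readmission, events in the gap count in both arms and the ratio in the illustration is 1.00.

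**The case against.** The strongest reply has four parts.

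1. *The 15-day rule does not define the outcome.* It selects cases for review, and section 6.1 describes no between-arm test. This stands. A reader might infer that outcome 8 is measured over 15 days from discharge, but section 2.4 does not say so. The mechanism does not depend on that window, since any readmission must follow discharge.

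2. *The control event is not lost.* Outcomes 1 and 2 are not limited to the time after discharge, outcome 10 reflects a prolonged birth stay, and section 3.2.1 records health-insurance numbers for eventual linkage to administrative data. So the reading that such an event goes wholly unrecorded in controls is not supported. What remains is that treatment given in the birth stay is not among the listed chart items, and that length of stay gives no reason for the stay.

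3. *The gap may be small.* Section 3.6 describes discharge at these times as not unusual, clinic-arm discharge is only an aim, and every participant has been judged fit for it before randomisation. This stands, and it is why no size can be claimed. With no gap, however, the trial would also not achieve the shorter stay it aims for.

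4. *Extra returns are a genuine effect of the assigned strategy, and counting rules belong in the SAP.* The first half is a fair choice of estimand and a good reason to keep plain readmissions. The second half holds for the window, but an SAP cannot analyse birth-stay treatment that was never abstracted.

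It is also tempting to quote the share of clinic-arm events that falls in the gap, 1/15 = 7% for 24 hours under a uniform rate, as the bias. It is not the bias under the 15-day rule, because the control window also closes later and the net difference is zero.

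**Conclusion.** The point holds as a cheap improvement. It does not show that outcome 8 is invalid or must be replaced. Readmissions and the DSMB count start at a moment that allocation shifts, and if early events are the more frequent the resulting bias runs against the clinic arm. The documents do not fix its size: they give neither the control stay nor the timing of events. It is nil without a gap, and about nil under a uniform rate with a window of 15 days after discharge. It is about 18% to 39% of control readmissions for a 24-hour gap, and 9.5% to 22% for a 12-hour gap, if the rate declines exponentially with a mean of 5 to 2 days. Those figures assume equal morbidity in both arms and that infants treated during the birth stay are not readmitted later for the same problem. Outcomes 1, 2 and 10 reduce the problem but do not remove it.

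**What to change.** - **Sections 2.4 and 4.3:** keep readmissions as listed. Add a between-arm comparison of hospital treatment of the infant or the mother, whether during the birth stay after randomisation or on readmission, up to a fixed day after birth (such as Day 30) in both arms.
- **Section 3.2.1:** add treatment given during the birth stay, with its timing, to the chart items.
- **Section 6.1:** report the DSMB readmission count by infant age, beside the added measure.

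The cost is one more item from a chart that is already abstracted and one more secondary analysis. No discharge or treatment rule changes.

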## 6.2 Participant information and consent

The Investigator or study staff will explain to each potential participant the aims, methods, reasonably anticipated benefits and potential risks of this study in written form and by verbal explanation in non-technical terms (lay language). After this explanation and prior to any trial related activity, participants will give their informed consent by completing the consent form. Both the participant and the Investigator (or study staff) must sign and date the form. The participant will receive a copy of the completed informed consent. The participants assigned to the clinic will receive a brochure with information on the location of the clinic and details of their appointment time.

## 6.3 Compensation

Women randomized to the intervention arm of the study will be reimbursed \$20 plus one parking token per visit (to a maximum of three visits) for costs associated with travel to the clinic.

## 6.4 Records retention

The trial related records will be retained for 10 years. Records will be kept to enable linkage of participants' identify to CRF data (master log). This includes sufficient information from hospital and clinic records such as original signed informed consent forms, contact information and completed surveys. After 10 years, all study records will be destroyed.

## **8 Evaluation tools**

### **8.1 Demographics**

### **8.2 Edinburgh Post Partum Depression Scale**

### **8.3 Breastfeeding Self Efficacy Scale**

### **8.4 Local Breastfeeding Complications Questionnaire**

### **8.5 Use of Resources Questionnaire**

### **8.6 Breastfeeding Questionnaire**

### **8.7 Mother Satisfaction Survey**

